### Sample size

Previous within-group design studies [35, 38] showed moderate to large pre-post effect strengths of the group meditation program. The expected effect size for wait-list controlled studies cannot be derived from within-group design studies. However, given the expectations that a wait-list control group of patients with chronic depression will not change over the waiting period, and that the additional individual treatment component may increase the efficacy of the group meditation treatment, we assume at least a moderate effect of f = 0.25 in comparison to the wait-list control group. A power analysis was computed using G-Power 3.1.9.2 [56], with repeated measures ANOVA (within–between interaction) with two measurement time points, a power of 0.80, a strict α error probability of 0.01, and a correlation among the repeatedly measured dimensions of r = 0.7 [57], resulting in a sample size of 34 (using effect size specification as in SPSS). Hence, including a supposed drop-out rate of 25%, at least 46 patients must be recruited for this study. In order to realize group treatments with traditional group sizes (8–12 participants), we decided to perform the trial with two rounds or *cohorts* with equal size, each with one treatment and one wait-list control group. During the first round of the trial, half of the participants (cohort 1) will be recruited, randomized, and receive treatment or be in the wait-list control group. This procedure will be repeated in the second round with the second half of the participants (cohort 2). As a result, we will have a total of four therapy groups (two times one treatment and one control group). Since we strive for balanced therapy group sizes, we will include 12 participants per therapy group, i.e., 4 × 12 = 48 participants in total.

We would like to mention that as a result of this procedure we will have a stratification variable “cohort”. Since this stratification variable will be included only for administrative reasons, we will not include it in our statistical models [58].

An additional power analysis with the same parameters as above but with three measurements (including intermediate measurements), four groups (including a two-level stratification variable), and a less strict α error probability of 0.05 resulted in a sample size of 28.

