### Statistical analysis

The primary outcome measure is pre-post (i.e., T0–T2) changes on the QIDS-C. Intention-to-treat analyses will be employed in this trial. For the statistical analysis of the primary outcome we will use a three-factor mixed-design ANOVA with two two-level between-subjects factors (treatment and CTQ-based stratifier) and a two-level within-subjects factor (time, T0 and T2) in the model. For our primary outcome, the group difference at T2, we will use a model with an interaction of treatment by time. An additional analysis including T1 will be performed using planned contrasts to examine changes in depression after group and individual treatment. We will use a repeated measures MANOVA including a time by treatment interaction to assess the effects of secondary outcomes, which we assume to be moderately inter-correlated, followed by univariate repeated measures analyses.

An intended aim was to detect mechanisms of change, which requires a mediation analysis. However, mediation analyses using structural equation analyses and latent growth curve analyses require a larger sample size, more measurement occasions of potential mediators than given in our study, and the control of confounding variables between mediators and outcome [88]. Therefore, exploratory regression analyses using pre-post differences in primary and secondary outcome after the meditation group treatment and the individual treatment will be performed to detect possible candidates for mediation analyses within future studies. Missing data will be handled using multiple imputation procedures. Data collected about adverse events and serious adverse events will be summarized by type and frequency, and regression analyses will be conducted to explore relations between adverse events and treatment. For statistical analysis, the computer program SPSS® (Statistical Package for Social Sciences, version 25) will be used.

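### The planned 34 patients rest on a between-arm difference of about 1.0 SD, which the Sample size section presents as a moderate effect

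*Protocol article*

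**What the plan says.** The Sample size section of the protocol article sets the effect first: "we assume at least a moderate effect of f = 0.25 in comparison to the wait-list control group". The reasons given include the expectation that "a wait-list control group of patients with chronic depression will not change over the waiting period". The calculation was run in G-Power "with repeated measures ANOVA (within–between interaction) with two measurement time points", with "a power of 0.80, a strict α error probability of 0.01" and "a correlation among the repeatedly measured dimensions of r = 0.7", "resulting in a sample size of 34 (using effect size specification as in SPSS". The section continues: "including a supposed drop-out rate of 25%, at least 46 patients must be recruited for this study". The target is then rounded up to 48, in four therapy groups of 12.

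The Statistical analysis section ties the primary question to the end of treatment: "For our primary outcome, the group difference at T2, we will use a model with an interaction of treatment by time".

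Neither section translates f = 0.25 into QIDS-C points or standard deviations, and neither reports the effect size on the SPSS scale.

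**The concern.** In a comparison of two group means, f = d/2, so f = 0.25 is d = 0.5, the usual moderate effect. In a two-arm, two-time-point interaction, the same f on the scale that also takes in the correlation stands for a much larger between-arm difference. The text uses the moderate label for the comparison with wait-list but takes its sample size from the interaction scale.

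The mention of the SPSS specification adds a second difficulty. On that scale the correlation is already contained in the effect size, so f = 0.25 taken at face value there does not give 34. The stated inputs, read literally, do not lead to the stated result.

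At stake is what the trial can be said to detect. A reader of the section would credit it with 80% power for a moderate advantage over wait-list.

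**Working it through.** **Inputs (Sample size section).** f = 0.25; two arms; two time points; r = 0.7; alpha 0.01; power 0.80; drop-out 25%; 48 planned. Equal arms are taken from the Design and setting section. All powers use the noncentral F distribution with 1 and N − 2 degrees of freedom. Raw SD means the SD of QIDS-C at one time point, taken as equal at T0 and T2.

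**1. Reproducing 34.**
- *Default scale.* λ = f² × N × 2/(1 − r) = 0.0625 × 2/0.3 × N = 0.4167N. Power is 0.773 at N = 30 and 0.808 at N = 32, so N = 32.
- *Same effect converted to the SPSS scale.* f(U) = 0.25 × √(2/0.3) = 0.645 and λ = f(U)² × (N − 2) = 0.4167(N − 2). Power is 0.777 at N = 32 and 0.812 at N = 34, so N = 34, the stated figure. Partial eta-squared is 0.4167/1.4167 = 0.29.
- *0.25 entered directly on the SPSS scale.* λ = 0.0625(N − 2). Power at N = 34 is 0.11, and 80% needs N = 194.

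The drop-out step is right: 34/0.75 = 45.3, which is 46 as an even total.

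**2. What the effect behind 34 means.** In a 2 × 2 interaction with f = 0.25, each cell mean departs from additivity by ±0.25 SD. The difference in change between arms is therefore 4 × 0.25 = 1.0 raw SD. As a check, the SD of change is √(2 × (1 − 0.7)) = 0.775 raw SD. A t-test on change then has λ = (N/4) × (1.0/0.775)² = 0.4167N, the same as on the default scale. With equal expected baselines under randomization and no change in controls, the T2 difference is also 1.0 SD.

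**3. Power if moderate means d = 0.5 at T2 (an assumption).** λ = (N/4) × 0.25/0.6.

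| Evaluable N | λ | Power, alpha 0.01, r = 0.7 | Difference detectable with 80% power |
|---|---|---|---|
| 34 | 3.54 | 0.21 | 0.96 SD |
| 36 (48 less 25%) | 3.75 | 0.23 | 0.93 SD |
| 48 | 5.00 | 0.34 | 0.79 SD |

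At r = 0.7 and alpha 0.01, 80% power for 0.5 SD would take 116 evaluable patients.

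**4. Sensitivity at N = 34, d = 0.5, alpha 0.01.** Power is 0.12, 0.15, 0.21 and 0.35 for r = 0.5, 0.6, 0.7 and 0.8. Adjusting for baseline by ANCOVA at r = 0.7 gives 0.26. Using N − 4 degrees of freedom, to allow for the CTQ stratifier in the model, changes 0.215 to 0.213. At alpha 0.05 and r = 0.7 power is 0.45. A difference of 0.8 SD has power 0.61 at alpha 0.01.

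**The case against.** The strongest reply is that nothing has been miscalculated. The protocol names f = 0.25 and the test, and on the converted scale power is 0.81 with 34 and 0.84 with 36. That stands. A reader might infer that 34 is an arithmetic error, and it is not.

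A reader might also infer that the trial's power is simply about 21% instead of 80%. The documents do not support that as a fact. The lower figure needs moderate to be read as 0.5 SD at T2. The comparison with wait-list invites this reading but does not compel it, because no SD or QIDS-C difference is given.

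Nor do they show that 194 patients were required. That number follows only from entering 0.25 directly on the SPSS scale, where r would play no part. Since r is reported and 34 results, this was evidently not done. What remains is that the section omits the converted value, so its inputs cannot be followed to its result.

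A large effect also has some support. The Background reports moderate to large pre-post effects in the first pilot and large ones in the second, and the protocol adds an individual component and assumes at least the stated effect. But the pilots were uncontrolled, and the Sample size section itself says that the expected effect cannot be derived from such studies. So 1.0 SD is not shown to be unreasonable, but it is not what the text says it assumes.

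Two further inferences should be left aside. The Statistical analysis section does not repeat alpha 0.01, but the Sample size section states it, and such detail is commonly left to an analysis plan. That a null result will be misread as ruling out a moderate benefit is speculation; no passage says so.

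**Conclusion.** The point holds as a misdescription of the effect size. The figure of 34 rests on a between-arm difference in change of 1.0 raw SD, equal to 1.0 SD at T2 under the protocol's own expectation for controls. That is a large effect labelled moderate. The stated 80% power does not carry over to a moderate two-group difference. If that means 0.5 SD, power at alpha 0.01 and r = 0.7 is 0.21 to 0.34 for 34 to 48 evaluable patients, and none of the variants checked at N = 34 comes near 80%. The 1.0 SD equivalence follows from the stated inputs, given equal SDs at T0 and T2. The power figures for 0.5 SD depend in addition on that reading of moderate. Design, test and recruitment target are unaffected.

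**What to change.** Keep 48 patients and restate the Sample size section:

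- Remove the word moderate from the effect-size assumption.
- Report the SPSS-scale effect as f(U) = 0.645 (partial eta-squared 0.29), derived from f = 0.25 and r = 0.7, so that the stated inputs lead to 34.
- Add a statement such as: *With 36 evaluable patients (48 less 25%), the trial has 80% power at two-sided alpha 0.01 to detect a difference of about 0.93 SD at r = 0.7 (0.79 SD if all 48 are analysed). Power for a difference of 0.5 SD is about 23% with 36.*

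The cost is wording only. No patients are added, which matters because the Trial status section reports that the last participant was recruited in April 2019. The downside is that the stated detectable effect becomes less favourable.

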### Participant recruitment process

Study participants are recruited in the Frankfurt metropolitan region through the Center for Psychotherapy at the Goethe University Frankfurt, self-help groups, psychosocial counseling centers, flyers, and advertisements on websites. In addition, we will recruit participants via press releases. Interested people will complete a brief telephone eligibility screening interview. Inclusion/exclusion criteria will be assessed by trained, independent clinicians using SCID-I and II [59, 60] and the Psychiatric Status Rating for Chronic Depression (PSR-CD) [61]. Since we intend to include a total of 48 participants and have two cohorts, for each cohort a total of 24 participants will be recruited for the trial.

### Randomization

Participants will be randomly and uniformly allocated to two test conditions. We suppose that differences in the individual history of childhood maltreatment may have an influence on the effectiveness of the treatment. Therefore, to prevent imbalances between treatment groups, the sample will be stratified based on the two-level-factor “reported adverse childhood experience” as measured before randomization by the Childhood Trauma Questionnaire [62]. Since we pursue the aim to inform participants about their allocation as soon as possible (see below), we decided to perform stratification and randomization as soon as half of the participants of one cohort (or one subcohort) have been enrolled. Thus, once 12 participants have been enrolled (subcohort 1 of 2), they are assigned to a stratum depending on their CTQ scores (“high level of childhood trauma/adversity” or “absence or low level of childhood trauma/adversity”). The CTQ cut-off values are set in advance. If odd numbers of participants are in the strata, the participant nearest the CTQ cut-off value will be assigned to the other stratum, despite not meeting the criteria for it. This procedure allows us to use random permuted blocks of even length (*n* = 2, 4, 6, 8, 10, or 12) in the strata. These steps will be repeated with subcohort 2 (of 2). Hence, within each of these strata, participants will be randomly assigned to the treatment or to the control condition, producing equal therapy group sizes.

We will send anonymized participant codes via e-mail to an independent statistician, who will conduct randomization. Randomization will be carried out with computer-generated random lists created using Microsoft Excel®.

### Blinding

Diagnosticians collecting observer rated measures will be blind to participant assignment as timing of assessments will be the same for all participants of a cohort. Blinding of diagnosticians should be maintained under all circumstances. To ensure that blinding is maintained, participants will be asked not to indicate their allocation status to the diagnosticians. Due to the design of the study, intervention blinding of participants and research workers, who also act as therapists, is not possible. The principal investigator is not blinded as he also implements the group therapies and individual therapies. Statistical analyses will be conducted by the authors, who will not be blinded or independent.

### Interventions

In our study, two approaches are to be combined in an approximately 4-month treatment program: a metta-based group meditation program focusing on the meditation of mindfulness and metta (eight sessions of 120 min each + one half-day retreat), and an individual CBT program (eight sessions of 100 min each) based on CBT and schema therapy that emphasizes the transfer of the meditation program into daily life. The metta-based group treatment has been tested in a pilot study and has been slightly modified for this trial. An individual subsequent CBT treatment including behavioral activation, cognitive restructuring and—optionally—elements from schema therapy has been added to this trial. The traditional concept of behavioral activation [63] was adapted to an interpersonal focus emphasizing self-confidence, positive social impact, and social interactions. Positive interpersonal behaviors are promoted based on personal values [64], which helps to create a more positive attitude to oneself and others in concrete actions. The intervention also involves the development of an accepting attitude towards negative emotions and cognitions [65], as well as actions involving benevolence to self and others [29]. The practice of combining these interventions has been done informally by our work group in several cases of chronically depressed patients from our pilot studies [35, 38] who had completed the studies but required additional treatment after termination of the study.

The mindfulness exercises are based on the manual of Segal, Williams, and Teasdale [66] and include a body scan exercise, sitting meditation, and the breathing space exercise. A shortened sitting meditation form is the basis of the metta meditation and the starting point of the meditation exercises. The breathing space exercise is used especially in stressful everyday situations for a more conscious perception of thoughts, feelings, and body sensations. It will also be used to help participants distance themselves from rumination. To achieve maximum acceptance among all participants, esoteric terms were avoided in the instructions where possible.

The individual treatment part of the present trial will build on the experience gained from a randomized controlled clinical trial with patients with recurrent depression [70]. In this previous study, an approach of combining individual setting elements of MBCT as well as Acceptance and Commitment Therapy (ACT) with activity scheduling and other behavioral techniques was applied [71]. If patients report adverse memories about their childhood or other distressing events arising from dysfunctional schemas, techniques from schema therapy are used (e.g., schema diary, imagery rescripting, and empty chair dialogues).

Individual treatment will be carried out by two approved, experienced therapists and three clinical psychologists who are at an advanced stage of their post-graduate training in CBT. All therapists have received training in the treatment manual.

The participants will also be asked to respond daily to short electronic questionnaires throughout the project period. The questionnaire asks about the mood, whether the participants have meditated and, if so, how long and how well it worked. For this, text messages are sent with web links to the questionnaires. This has the function of a reminder but also of a meditation diary. In addition, these questionnaires will be evaluated weekly and give the study team and the therapist feedback on how the participants are adhering to the treatment. The questionnaires are located on the “unipark” platform and participants are asked to use their individual anonymized code to ensure protection of private participant data.

### Outcome measures

Proposed psychological outcome measures are as follows.

#### Primary outcome measure

Severity of depressive symptoms as measured by the Quick Inventory of Depressive Symptomatology (QIDS-C) [72]

To comply with aims 1 and 2 (baseline measurement after randomization and as close to the beginning of the group as possible), we would have to perform the randomization shortly before the start of the group program. We decided to give aim 3 more weight and thus drop aim 2. As a result, after the randomization and before the baseline measurement participants are aware of their allocation. Knowing their allocation may motivate participants to report better or worse scores in the baseline outcome measures. We note this is not ideal and will discuss it in the primary trial publication.

Time points of outcome measures will be anchored to baseline measures, which take place within 2 weeks before the beginning of the group treatment. All further outcome measures (i.e., T1, T2, and T3) will take place at fixed time points after baseline measures, as defined in Table 1, i.e., 9, 26, and 52 weeks after baseline measures.

[figure not shown]

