### Hypotheses and research questions

The primary outcome measure in this trial is the difference in the severity of depressive symptoms between the two groups. The main research question is: Does the combination of group meditation and individual CBT lead to significantly greater reduction in depressive symptoms compared to a wait-list control condition after overall completion of treatment (at T2)?

The previous data suggest that, at least in the short term, a stabilization of mood improvements is possible by maintaining a regular meditation practice [38]. So far, little research has focused on the maintenance of therapy success of group meditation programs for PDD. Therefore, a secondary question is: Does the effect in the treated group appear to be maintained at the 6-month follow-up?

In addition to the primary outcome measure, further changes will be recorded regarding specific effect parameters related to the two treatment components (meditation and CBT). The aim is to enable an intermediate measurement to identify changes in the two phases of treatment. Therefore, another secondary question is: Compared to control group, are there any significant changes in patients’ mindfulness, benevolence, rumination, emotion regulation, social connectedness, social motivation, and behavioral and cognitive avoidance (a) after the group meditation program and (b) after completion of the overall treatment?

The design of this study does not allow us to test the separate effects of both components, group meditation and individual CBT, which would require a different design. Furthermore, we will not be able to conduct adequate mediation analyses as the statistical power would not be sufficient to do so. However, exploratory analyses will be conducted to examine whether pre-post changes in depression in the group meditation program are associated with changes in the subsequent individual treatment.

In addition, in line with research indicating that mindfulness-based meditation is associated with changes in emotion regulation, especially acceptance and revaluing [32], and the reduction of avoidance [55], we will explore whether changes in the variables “emotion regulation”, “behavioral avoidance”, and “cognitive avoidance” are associated with the primary outcome at post-treatment.

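### The primary treatment-by-time contrast gives full weight to a baseline taken after participants know their arm, so a shift confined to T0 passes entirely into the estimated effect

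*Protocol article*

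**What the plan says.** The end of the Secondary outcome measures section sets out three competing aims and gives up the one that would place baseline before randomisation. It states the result plainly: "after the randomization and before the baseline measurement participants are aware of their allocation". It names the risk, "Knowing their allocation may motivate participants to report better or worse scores in the baseline outcome measures", and the response to it, "We note this is not ideal and will discuss it in the primary trial publication". Under Randomization, each subcohort of 12 is allocated once enrolled so that participants learn their arm early. T0 follows within the two weeks before the group programme starts.

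The Statistical analysis section defines the endpoint: "The primary outcome measure is pre-post (i.e., T0–T2) changes on the QIDS-C". The model has "a two-level within-subjects factor (time, T0 and T2) in the model", and the test is described this way: "For our primary outcome, the group difference at T2, we will use a model with an interaction of treatment by time". The Hypotheses section says that "The primary outcome measure in this trial is the difference in the severity of depressive symptoms between the two groups", then asks whether symptoms fall more under treatment by T2.

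QIDS-C raters are blinded (Blinding; Data collection). Participants are not.

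**The concern.** When baseline precedes allocation, the T0 means of the arms differ only by chance. The difference in change and the difference at T2 then estimate the same quantity. Here the protocol itself says allocation may move T0, so the two can differ systematically. The Statistical analysis section nevertheless uses both descriptions for the primary outcome, and the test it fixes is the one that subtracts T0 with a coefficient of one.

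The error can go either way. If treated participants present as worse at T0 for reasons that have gone by T2, a benefit appears where none exists. If wait-list participants present as worse at T0 out of disappointment, their later return to usual looks like improvement and hides part of a real benefit.

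**Working it through.** **Inputs.** From Sample size: r = 0.7, alpha 0.01, f = 0.25, power 0.80, 34 evaluable, 25% dropout, 48 planned in equal arms. The protocol gives no QIDS-C SD and no shift size, so results are in SD units and the shift s is an assumption, shown over a range. The CTQ factor in the planned model is ignored for simplicity.

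**The plan's own figure.** For the within–between interaction with 2 groups and 2 times, use a noncentral F with 1 and N − 2 degrees of freedom.
- With λ = f²(N − 2)·2/(1 − r), N = 34 gives λ = 0.0625 × 32 × 2/0.3 = 13.33 and power 0.812. N = 33 gives 0.795. So 34 is reproduced.
- With N in place of N − 2 (the G*Power default), 32 suffices, and 34 gives 0.839.
- 34/0.75 = 45.3, rounded up to 46, as stated.

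The sample size is not in question. The point is bias.

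**Pass-through.** Interaction = (T2 treated − T2 control) − (T0 treated − T0 control).

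| Shift of size s | Interaction | ANCOVA on T0 (slope 0.7) | T2 without T0 |
|---|---|---|---|
| At T0 only | −s | −0.7s | 0 |
| Same at T0 and T2 | 0 | s − 0.7s = 0.3s | s |

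A simulation with a T0-only shift of 0.3 SD, 24 per arm and no true effect gave −0.298, −0.208 and 0.001 for the first row. A persistent shift gave 0.002 for the interaction.

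**False-positive rate of the planned test, T0-only shift, no true effect.** SE of the difference in change = √(2(1 − 0.7)) × √(2/n per arm). This is 0.266 SD at 17 per arm and 0.224 SD at 24. Rejection rates come from the noncentral t with noncentrality s/SE. For example, 0.2/0.224 = 0.894 on 46 df gives 4.4%.

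| s (assumed) | 17 per arm, nominal 1% | 24 per arm, nominal 1% | 17 / 24 per arm, nominal 5% |
|---|---|---|---|
| 0.1 SD | 1.5% | 1.7% | 6.5% / 7.2% |
| 0.2 SD | 3.2% | 4.4% | 11.3% / 14.1% |
| 0.3 SD | 6.6% | 10.0% | 19.5% / 26.0% |

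At 0.3 SD, 24 per arm and nominal 1%, the rate is 5.8% if r = 0.5 and 36.9% if r = 0.9.

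**ANCOVA under the same shift.** SE = √(1 − 0.49) × √(2/24) = 0.206 SD at 24 per arm, and the bias is 0.7s. At nominal 1% the rates are 2.8% for 0.2 SD and 5.6% for 0.3 SD.

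**Price of leaving T0 out.** Power at alpha 0.01 for a 1 SD difference (4 × 0.25, the difference in change that f = 0.25 implies under the G*Power default), with T0 unaffected:

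| Analysis | 17 per arm | 24 per arm |
|---|---|---|
| Interaction | 0.839 | 0.958 |
| ANCOVA on T0 | 0.901 | 0.982 |
| T2 only, unadjusted | 0.575 | 0.777 |

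**The opposite case.** If a 0.3 SD reporting shift persists to T2 with no treatment effect, the T2-only test at 24 per arm has noncentrality 0.3/0.289 = 1.04 and rejects 5.8% of the time at nominal 1%. The interaction stays at 1%.

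**The case against.** The strongest reply is that participants know their arm at T2 as well. If hope or disappointment colours both interviews equally, it cancels from the change score and remains in full in a T2 comparison. This stands. A reader might infer that every allocation-induced shift biases the planned test, or that a T0-free analysis is unbiased. The documents support neither, because they do not say whether such a shift would last.

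Second, the authors disclose the problem and give a retention reason for the order of events. Also true: nothing is hidden. But the protocol fixes both the post-allocation T0 and a contrast that weights it fully, and disclosure does not alter that contrast. For this reason the point is more than detail left to an analysis plan.

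Third, blinded clinicians rate the QIDS-C. This may shrink the shift. It cannot exclude it, because the rating draws on what an unblinded participant reports. The self-report secondary outcomes, also tested by time-by-treatment interaction, lack even that protection.

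Fourth, the two descriptions of the primary outcome may be loose wording. For the Hypotheses section that is fair, since its wording fits either target. In Statistical analysis the phrase and the test appear in one sentence, and they differ by exactly the T0 shift.

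Finally, one might want a rule that calls the result baseline-dependent whenever analyses with and without T0 disagree. If disagreement means significance, the weaker model would trigger it often without any shift: 0.777 against 0.982 power at 24 per arm, and 0.575 against 0.901 at 17.

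**Conclusion.** The concern holds for a shift present at T0 and absent at T2. Such a shift enters the planned primary effect in full, and nothing planned in the protocol limits or examines it. This is algebra and needs no assumption about size.

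The consequence does depend on size, which is unknown. For assumed shifts of 0.1 to 0.3 SD at r = 0.7, the nominal 1% error becomes 1.5% to 6.6% with 34 evaluable and 1.7% to 10% with 48. With 25% dropout foreseen, the lower set is as relevant as the upper. A small shift does little harm. The direction is also unknown, so the trial could overstate or understate the benefit.

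No analysis of these data is safe against both a transient and a persistent shift. ANCOVA on T0 is the compromise: 0.7 of a transient shift, 0.3 of a persistent one, and better precision than the change score. The point is worth acting on, but it does not invalidate the trial.

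**What to change.** - State one primary estimand: the between-group difference in QIDS-C at T2. Estimate it by ANCOVA on T0 with the CTQ stratum. Say that this reduces the pass-through of a T0-only shift to about 0.7 at r = 0.7 and does not remove it.
- Add one named sensitivity analysis: T2 QIDS-C on treatment without T0, adjusted only for variables measured before randomisation. The CTQ qualifies (Randomization). The PSR-CD is used at eligibility (Participant recruitment process), but the text does not say that an analysable score is kept, so include it only if one was recorded before allocation. Cohort need not be added, as Sample size gives a reason for leaving it out.
- Report T0 means by arm.
- Set the two estimates and confidence intervals side by side. Do not compare their significance or attach a label to disagreement.
- State that the T0-free model is less powerful (about 0.78 unadjusted against 0.98 for ANCOVA at 24 per arm, 1 SD, alpha 0.01) and is free of this bias only if the shift has gone by T2.

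Recruitment is complete, so the timing of T0 cannot change. The cost is analysis wording and one extra model on data already planned. Because the analysts are not blinded (Blinding), date the change before any comparison of the arms is run.
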